| Pregnancy Test                                                                               | X                                  |                                                     |                               |                              |                               |                              |                               |                               |                               |                               |                                                        |
| Mid-nasal swab or saliva for SARS-CoV-2 confirmation and viral load assessment (D0, and D14) | X                                                |                                                     |                               |                              |                               |                              |                               | X                             |                               |                               |                                                        |
| Mid-nasal swab or saliva for biobanking deposit (D3, D7 and D10)                             |                                                  |                                                     |                               | X (D3)                       | X (D7)                        |                              | X                             |                               |                               |                               |                                                        |
| Concomitant medications                                                                      | X                                                |                                                     |                               | X (D3)                       | X (D7)                        |                              | X                             |                               |                               |                               |                                                        |

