| 
 
To test whether any of the experimental interventions is associated with decreased viral shedding from self-collected nasal swabs over 14 days: Day 1, Day 10 and Day 14 (+/-1 days)
 
 | 
 
Proportion of days with SARS-CoV-2 detected from mid-nasal swabs by PCR
 
Change in viral load on day 10 and day 14 after randomization from baseline
 
                                                                                                                                                                                                                                                                                                                                                                                                                                                                                                                                             |
| 
 
To test the quality-of-life (QoL) of experimental interventions for treatment of high-risk outpatients with SARS-CoV-2 infection
 
                                                     | 
 
Change in quality of life measured by Eq-5D-5L from baseline
 
                                                                                                                                                                                                                                                                                                                                                                                                                                                                                                                                                                                                                                             |

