#### **10.1.2. Day 1 Through Day 14**

The participant will do the following every day from Day 2 through Day 14 (unless stated otherwise), inclusive:

- Take study therapy (for a total treatment of 10 days of treatment)
- Tolerance towards the assigned therapy
- Confirmation of adherence to study therapy dosing (Day 10)
- Daily dosing time from the day prior
- Reporting of adverse events
- Cardiac measurement using Kardiamobile monitors (Day 3, Day 7, Day 10, and Day 14)
- Pulseoximeter measurements (Day 3, Day 7, Day 10, and Day 14)

| Harmonized protocol document                                                          |
|---------------------------------------------------------------------------------------|
| Short title: Outpatient Management of SARS-CoV-2 for High-Risk Adults in LMICs |

- Measurement of heart rate (pulse oximeter) at rest after the participant remained seated at rest for 5 minutes
- Review of clinical symptoms and hospitalization
- WURSS-11 survey for dyspnea

A study team member will be available via Telehealth, text messaging, or telephone to provide support for completion of study procedures. Participants will be clinically assessed for signs and symptoms of respiratory distress and will have in person assessment of AEs. As needed, additional contact with the study clinician or staff will be conducted at the request of the participant (e.g., if developing concerning symptoms or an adverse event) or if needed to clarify study procedures or follow-up symptoms.

The health care provider will make home-visits to collect nasal-swabs or saliva samples for RT-PCR on Day 3, Day 7, Day 10, and Day 14. These samples collected on Day 14 will be used to analyse the viral shedding related outcomes. Other samples collected on Day 3, Day 7 and Day 10 will be stored for a biobanking deposit.

A study team member will be available via Telehealth, text messaging, or telephone to provide support for completion of study procedures.

Clinical outcomes will be confirmed through the electronic health record, if possible.

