**10.1.7. Day 2 Through Day 13**

The participant will do the following every day from Day 1 through Day 13, inclusive:

- Collect mid-nasal swab for PCR on Day 3, Day 5, Day 7 and Day 10. (Swab collection may be decreased to Day 5 and Day 10 in participants where multiple swabbing is not feasible.)
- Take study therapy (as assigned)
- Complete Daily Survey (online, telephone, or text messaging). This Survey will include confirmation of adherence to study therapy dosing and daily swab collection, concomitant medication review, AEs, and symptoms review and objective measures including SpO2, respiratory rate, temperature and pulse. In addition, the Transitional Dyspnea Survey will be completed.
- *If in DBS Sub-study, collect DBS samples for analysis of concentration of assigned experimental intervention at any time during this period (1 to 5 times) after study drug dosing has commenced. No more than 1 sample per day should be collected.*

A study team member will be available via Telehealth, text messaging, or telephone to provide support for completion of study procedures. The driver will collect the swabs as required.

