#### **10.1.9. Day 14**

The participant will do the following on Day 14:

- Collect mid-nasal swab for PCR (May be omitted in participants where multiple swabbing is not feasible).
- Complete Daily Survey (online, telephone, or text messaging). This Survey will include confirmation of adherence to study therapy dosing and daily swab collection, concomitant medication review, and symptoms review and objective measures including SpO2, temperature and pulse.
- 
- *If in DBS Sub-study, collect DBS samples for analysis of concentration of assigned experimental intervention, if not already collected.*

A study team member will be available via Telehealth, text messaging, or telephone to provide support for completion of study procedures.

Clinical outcomes will be confirmed through the electronic health record, if possible.

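### The share-of-days viral shedding endpoint cannot be measured as named: swabs are not daily, the sampling days conflict, and the score depends on which days are swabbed

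*Protocol*

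**What the plan says.** The endpoint "Proportion of days with SARS-CoV-2 detected from mid-nasal swabs by PCR" appears in Protocol Section 4.1 and in the Synopsis table of objectives and endpoints. It sits under an objective on shedding from self-collected swabs "over 14 days: Day 1, Day 10 and Day 14 (+/-1 days").

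Other sections give other sampling days:

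- **Section 2.1 (Schedule of Activities)** has two separate rows: "Mid-nasal swab or saliva for SARS-CoV-2 confirmation and viral load assessment (D0, and D14") and "Mid-nasal swab or saliva for biobanking deposit (D3, D7 and D10").
- **Section 10.1.2** agrees with that split: "These samples collected on Day 14 will be used to analyse the viral shedding related outcomes", and "Other samples collected on Day 3, Day 7 and Day 10 will be stored for a biobanking deposit".
- **Section 11.1.1** has samples taken on Days 1, 3, 7, 10 and 14 and tested for the virus.
- **Sections 10.1.6, 10.1.7 and 10.1.9** have swabs for PCR on Day 0, on Days 3, 5, 7 and 10, and on Day 14. Section 10.1.7 adds: "Swab collection may be decreased to Day 5 and Day 10 in participants where multiple swabbing is not feasible". Section 10.1.9 has, for Day 14: "Collect mid-nasal swab for PCR (May be omitted in participants where multiple swabbing is not feasible").

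Section 4.1 also has a separate viral clearance endpoint, with clearance defined by a single negative swab, and an endpoint on change in viral load at Days 10 and 14.

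**The concern.** A share of days needs to know, for each day, whether virus was present. Here that is known on at most six days out of fourteen, unequally spaced, and possibly on different days in different patients. Early samples are nearly always positive: patients are randomized after PCR confirmation, and those who test negative are screening failures (Section 10.1.1). Late samples need not be. The mix of early and late swabs therefore moves the score on its own. Patients with the same course of shedding can score differently, and patients with different courses can score the same. What is at stake is whether this secondary endpoint can be interpreted at all, and whether it can register a shortening of shedding.

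**Working it through.** The protocol gives no sample size, event rate or power for this endpoint, so there is no stated figure to reproduce. The check is a direct count.

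**Inputs from the protocol.** The five swab sets in the table below.

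**Assumptions for illustration.** Shedding is continuous up to a last positive day L, PCR is without error, and all samples in a set are assayed. L is assumed at 4, 8 and 11 to show a range; the protocol gives no distribution of shedding times.

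**Formulas.** True share = L/14. Score = (number of sampled days not later than L) / (number of sampled days).

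| Swab days (source) | L = 4, true 4/14 = 29% | L = 8, true 8/14 = 57% | L = 11, true 11/14 = 79% |
|---|---|---|---|
| 1, 10, 14 (Section 4.1) | 1/3 = 33% | 1/3 = 33% | 2/3 = 67% |
| 0, 14 (Sections 2.1 and 10.1.2) | 1/2 = 50% | 1/2 = 50% | 1/2 = 50% |
| 1, 3, 7, 10, 14 (Section 11.1.1) | 2/5 = 40% | 3/5 = 60% | 4/5 = 80% |
| 0, 3, 5, 7, 10, 14 (Sections 10.1.6, 10.1.7, 10.1.9) | 2/6 = 33% | 4/6 = 67% | 5/6 = 83% |
| 0, 5, 10 (same sections, reduced, Day 14 omitted) | 1/3 = 33% | 2/3 = 67% | 3/3 = 100% |

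One patient's score therefore ranges over 33% to 50% at L = 4, 33% to 67% at L = 8, and 50% to 100% at L = 11, through the swab set alone.

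**The two-sample set.** With Days 0 and 14, a patient positive at baseline scores 1/2 if negative on Day 14 and 2/2 if positive. The score equals 0.5 + 0.5 × (Day 14 positive), so it carries only the Day 14 result.

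**Response to a treatment effect.** Suppose the last positive day moves from 9 to 6, a true difference of 3/14 = 21 percentage points.

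- Days 1, 10, 14: 1/3 − 1/3 = 0.
- Days 0, 14: 1/2 − 1/2 = 0.
- Days 0, 5, 10: 2/3 − 2/3 = 0.
- Days 1, 3, 7, 10, 14: 3/5 − 2/5 = 20 points.
- Days 0, 3, 5, 7, 10, 14: 4/6 − 3/6 = 17 points.

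Whether the effect shows depends on which section's schedule is followed.

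**The case against.** The strongest reply is that the wording is merely loose. The objective names its assessment days, so the natural reading is the share of those swabs that are positive, and the choice of denominator can be left to the statistical analysis plan (SAP). On a fixed schedule of Days 1, 3, 7, 10 and 14 the score tracks the true share well (60% against 57% at L = 8, 80% against 79% at L = 11). The option to reduce swabbing appears only in a visit block that fits poorly with the rest of the Brazil text: Section 10.1.11 reimburses participants on Day 14, whereas Section 13.1 says there is no reimbursement in Brazil.

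Part of this stands. A SAP may set the denominator. But it cannot supply days that were not sampled, and the conflict over sampling days is in the protocol itself. The visit block with the reduced option sits under the heading for Brazil. If it is set aside, Sections 2.1, 4.1, 10.1.2 and 11.1.1 still disagree. The daily survey in Sections 10.1.6, 10.1.7 and 10.1.9 does refer to daily swabs, but Sections 10.1.7 and 10.1.9 name the swab days, and none of the three schedules daily collection.

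Four stronger readings are tempting, and the document does not support them:

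- **Unsampled days count as virus-free over a denominator of 14.** That would understate shedding grossly, but no section divides by 14 or says how unsampled days are treated.
- **The reduced schedule leaves only two swabs.** Section 10.1.6 also collects a baseline swab on Day 0, so the reduced set is Days 0, 5 and 10, and clearance after Day 8 scores 67%, not 50%.
- **The comparison between arms is biased.** The schedule options apply to all arms. Bias would need the feasibility of swabbing to differ by arm, which is conceivable because full blinding is not feasible (Section 7.5) but is not shown.
- **A better endpoint would recover the lost sensitivity.** On Days 1, 10 and 14, a patient last positive on Day 1 and one last positive on Day 8 look the same under any analysis.

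**Conclusion.** The point holds. The endpoint cannot be measured as named, and read as a share of sampled days it depends on the swab set: 33% to 67% for a patient whose true share is 57%. Under Sections 2.1 and 10.1.2 it reduces to Day 14 positivity. The figures rest on assumed last positive days, continuous shedding and error-free PCR. The dependence on the swab set does not rest on any one value of L.

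The harm is a measure that is hard to interpret and, on the sparse schedules, insensitive. The endpoint is secondary and the primary analysis does not use it. The change should be made, but the trial's main conclusion does not depend on it.

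**What to change.** 1. Reconcile the swab days, and which samples are assayed and which only stored, across Sections 2.1, 4.1, 10.1.2, 10.1.6, 10.1.7, 10.1.9 and 11.1.1.
2. Replace the endpoint in Section 4.1 and the Synopsis by one of:
   - the proportion PCR-positive at fixed common days, namely Day 10 and Day 14. Day 10 is the firmer of the two, because every schedule collects it, including the reduced one. A Day 14 swab that was omitted should be treated as missing, not as negative; or
   - time to first negative swab, interval-censored between the last positive swab before it and that first negative swab, and right-censored at the last swab if none is negative. This keeps the protocol's own definition of clearance by one negative swab. A requirement for a sustained negative would depart from that definition, and could not be confirmed when the first negative is the last swab.

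No new samples are needed. Day 10 samples that Sections 2.1 and 10.1.2 mark for storage must be assayed, which the existing Day 10 viral load endpoint already requires. The proportion of days is no longer reported. The change removes the dependence on how many swabs a patient gave and when. It does not recover differences in shedding that fall between sparse swabs.

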## 5. Study Design

### 5.1. Overall Design

The overarching goal of this study is to assess the effectiveness of interventions on important clinical and viral outcomes among high-risk adult outpatients with SARS-CoV-2 infection to inform public health control strategies.

This is an international multi-center adaptive randomized platform trial for the treatment of SARS-CoV-2 infection in high-risk adults not requiring hospital admission.

Initially, the Brazil study will enrol 492 patients per arm with high-risk for hospitalization and LRTI progression at baseline who are PCR-confirmed SARS-CoV-2 infection.

In Brazil for TOGETHER 2, the trial will start with three arms:

- **Placebo:** Placebo pills acid 1000 mg orally twice daily for 1 day then 500 mg orally twice daily for 9 days
- **Lopinavir/ritonavir (LPV/r):** LPV/r 800 mg-200 mg orally twice daily x 1 day, then 400 mg-100 mg twice daily for an additional 9 days
- **Hydroxychloroquine (HCQ):** 800mg HCQ per day (2 HCQ tablets) for the first day followed by 400mg per day an additional 9 days (1 HCQ tablet)

Other chloroquine-based therapies, antiviral therapies, azithromycin, and other affordable candidate drug regimens that can be repurposed for COVID-19 may also be considered for this trial. The decision to add new therapeutic strategies will be made based on external findings with consultations of the local stakeholders. Therapies that can be repurposed for COVID-19 will be prioritized since they offer more affordable and scalable therapeutic options for LMICs. The added arm will be tested with standardized eligibility criteria, outcomes, and measurements, as the other experimental interventions.

An independent data and safety monitoring board (DSMB) will be convened for this study with expertise in COVID-19 or respiratory viruses and emerging epidemics as well as biostatistics. The purpose of the DSMB is to monitor the study for operational futility, social harms, and efficacy. The DSMB will also review the blinded sample size re-assessment plan, proposed sample size changes, and make recommendations on the allocation ratio, in case the new intervention arms are added. If additional data emerge on alternative effective agents, the protocol could be modified through an amendment to alter its sample size and evaluate alternative therapies.

A blinded sample size re-assessment will be done to potentially increase the sample size target during the trial, should a lower control event rate (CER) and/or higher drop-out rate be observed. The decision on the timing of the sample size re-assessment will be made by the independent DSMB during the trial based on the observed recruitment rate. The DSMB will also decide on a possible interim analysis during the trial after the sample size re-assessment based on the information on the observed recruitment rate, the CER, the drop-out rate, and the final sample size target, if applicable.

The decision for interim analysis will be made in a blinded manner (e.g., based on pooled number of events). The interim monitoring plan (written by the Study Statistician) will define monitoring bounds to maintain the two-sided type I error rate at the desired 5% (e.g. 97.5% or higher

| Harmonized protocol document                                                          |
|---------------------------------------------------------------------------------------|
| Short title: Outpatient Management of SARS-CoV-2 for High-Risk Adults in LMICs |

probability of superiority over the control group). Should a new experimental candidate be added during the trial, allocation ratios will be adapted to favor the new arm.

If additional data emerge on alternative potentially effective agents for SARS-CoV-2, additional arms can be added to the study as a new intervention appendix to the protocol. The standardized operating procedures and comprehensive statistical analysis plans will allow for integration of new arms.

### **5.1.1. Study Execution for Brazil**

This study will be carried in two stages: *Internal Pilot and Main Stages*

Due to the rapid evolution of the COVID-19 pandemic and the challenge that public health systems will face to respond to this devastating infection, there are several aspects related to the feasibility of the study that need to be evaluated as soon as we start implementing it.

The aim of the internal pilot phase is to assess any unpredictable feasibility problems and resolve them to improve the overall success of the research. In particular, we will assess issues related to drug recruitment, consent, availability and administration, data collection and recording. This will involve about 18-20 patients in total. There will be no statistical analysis at the end of the pilot stage. The pilot and main stages will be operationally connected with the patients enrolled in the pilot stage will be transferred to the main stage during which the recruitment efforts will be amplified.

The pilot stage will start with two arms: HCQ and placebo, with LPV/r possibly being added if the drug supply becomes available during the pilot stage.

The main stage will begin with three arms: HCQ, LPV/r, and placebo. Safety profile of the monotherapy arms will be tested after being administered for 100 patients per arm. This will be reviewed internally and externally with AbbVie. If adequate safety profile is observed in both monotherapies, combined arm of HCQ + LPV/r will be added into the TOGETHER 2 with permission from AbbVie.

With the time required to review the safety profile of HCQ and LPV/r monotherapy with AbbVie, (assuming adequate safety profile) the fourth arm of combined HCQ + LPV/r will likely be introduced into the trial after enrolment of 165 per arm has already been randomized to the three initial groups of placebo, HCQ, and LPV/r.

For the clinical evaluation of HCQ + LPV/r arm versus placebo, we will use unequal allocation of 3:1 (165 for combined arm and additional 55 for placebo arm) and will incorporate the previously placebo control data by borrowing the individual treatment effects of HCQ and LPV/r versus placebo as empirical prior for the clinical evaluation of the combined arm.

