| 
 
To test the efficacy of experimental interventions to prevent progression to LRTI, among persons with SARS-CoV-2 infection who are at high risk of progression
 
To test the efficacy of experimental interventions to reduce SARS-CoV-2 viral shedding
 
 | 
 
LRTI, defined by SpO2<93% or decline from baseline of 6% in 2 measurements at least 2 hours apart. Initially, the trial is statistically powered for this endpoint in high-risk population.
 
Proportion of persons with clearance of SARS-CoV-2 from nasal swabs or saliva, defined as 1 negative swab
 
 |
| 
 
To test the safety and adherence of experimental interventions for treatment of high-risk outpatients with SARS-CoV-2 infection
 
                                                                                                                                | 
 
Serious adverse events (including death, hospitalization) and adverse events resulting in treatment discontinuation up to 28 days
 
Proportion of non-adherent patients with interventions
 
                                                                                                                                   |
| 
 
To test whether any of the experimental interventions has an effect on hospitalization and mortality among persons who become hospitalized with COVID-19 disease (continued from primary outcome)
 
                                                              | 
 
Proportion hospitalized for COVID-19 progression
 
Days of hospitalization
 
Mortality for any causes after randomization up to 90 days
 
Mortality due to pulmonary complications
 
Mortality due to cardiovascular complications
 
                                                                      |

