### 7.5. **Blinding**

As there are multiple intervention regimens with different dosing schedule and route that make blinding for patients and clinicians will not be feasible. The medications are not identical-appearing and dosing is different for the active agents so blinding will operate in different ways across those involved in the study. This study will preserve blinding for the laboratory testing and study statisticians.

- The bottle of medication they receive will not identify the treatment allocation, only the number and frequency of pills to be taken. However, full blinding of patients will likely not be possible.
- While the study medication will be dispensed directly to participants, full blinding of the treating clinicians will not be feasible given that there are multiple intervention regimens.
- Laboratory testing for viral shedding will be blinded, as laboratory staff will not be informed of randomized assignment. The viral shedding endpoint of the trial is an objective one, unlikely to be altered by unmasking, should it occur.
- Study pharmacy staff will be unblinded, as they will prepare the study medication.
- The study statistician will be blinded for analysis purposes.

LPV/r and other regimens have a different dosing schedule and a different shape but study clinicians will not see the study medication, to mimic some blinding.

The participants will be blinded to their randomization group once assigned. At enrollment, the unblinded Study Pharmacist will use the randomization code revealed at the point of randomization to provide the participant with their group assignment and dispense the allocated study medication in a bottle marked with the study label. The medication and medication information, mid-nasal swabs sufficient to complete the study procedures, *DBS sampling kit, if within the sub-study*, and study instructions will be provided to the participant.

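### The planned safety review at 100 patients per arm would show by-arm hospitalisations and deaths, which largely overlap the primary endpoints, to the trial team and an outside company, with no DSMB or firewall named in that step

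*Protocol*

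**What the plan says.** Section 5.1.1 sets a checkpoint in the main stage: "Safety profile of the monotherapy arms will be tested after being administered for 100 patients per arm". It then names the reviewers: "This will be reviewed internally and externally with AbbVie". The decision rule follows: "If adequate safety profile is observed in both monotherapies, combined arm of HCQ + LPV/r will be added into the TOGETHER 2 with permission from AbbVie". Randomisation does not pause, because the combination arm "will likely be introduced into the trial after enrolment of 165 per arm has already been randomized to the three initial groups". The step mentions no DSMB, independent statistician or restriction on who sees the data.

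The safety endpoint in Section 4.1 is "Serious adverse events (including death, hospitalization) and adverse events resulting in treatment discontinuation up to 28 days". Section 11.2.4 counts any inpatient hospitalisation and any death as serious. The primary endpoints in Section 4.1 are COVID-19 hospitalisation (or clinical worsening where no bed is available) and death from COVID-19 complications up to 90 days.

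Elsewhere interim data are guarded. Section 5.1 convenes an independent DSMB, calls the sample size re-assessment blinded, and says of any interim analysis: "The decision for interim analysis will be made in a blinded manner (e.g., based on pooled number of events". Section 7.5 adds: "This study will preserve blinding for the laboratory testing and study statisticians". On the DSMB's remit, Section 5.1 says: "The purpose of the DSMB is to monitor the study for operational futility, social harms, and efficacy". The Version 3 text on adding treatment arms (listed as 7.10 in the amendment pages) also lets the DSMB assess safety and futility, at monthly meetings or at any time.

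**The concern.** In an outpatient COVID-19 trial with hospitalisation as a primary endpoint, safety and efficacy cannot be kept apart by calling one table a safety table. Whoever reads serious adverse events by arm reads most of the primary outcome by arm.

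Three features make this matter here. Section 7.5 accepts that patients and treating clinicians cannot be fully blinded. Part of the primary endpoint, clinical worsening when a bed is not available, is open to judgement. And Section 5.1.1 plans to use the HCQ and LPV/r effects against placebo as the prior for the combination arm, so people who have seen by-arm outcomes would help decide whether to open an arm whose analysis reuses those data.

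Knowing an individual's treatment does not reveal how the arms are doing; this review would. Recruitment, endpoint judgement and later choices about sample size, interim timing and added arms could then follow an early trend, and the company whose permission is needed would hold interim results of a running trial.

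**Working it through.** The protocol gives no figure for this step to reproduce. The check sets the provisions side by side and then sizes the exposure.

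**Is the review by arm?** Yes. Section 5.1.1 requires an adequate profile in both monotherapies, so each must be judged separately. Pooled data could not answer that question.

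**How far do the safety data overlap the primary outcome?**

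| | Safety data | Primary endpoints |
|---|---|---|
| Hospitalisation | any inpatient stay (11.2.4) | for COVID-19 (4.1) |
| Death | any death (11.2.4) | COVID-19 complications (4.1) |
| Worsening without admission | only if otherwise serious | counted when no bed is available |
| Horizon | to day 28 (4.1 safety endpoint) | mortality to day 90 |

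The two are not identical, but COVID-19 hospitalisations and COVID-19 deaths to day 28 fall in both.

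**How many events?** Inputs from Section 12.1: control event rate 20%, relative risk reduction 27.5%. Expected hospitalisations per 100 patients with complete follow-up:

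- no effect: 100 × 0.20 = 20
- effect as designed: 100 × 0.20 × (1 − 0.275) = 14.5

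**How early?** Both targets are taken as Section 12.1 states them.

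- 100/492 = 20.3%, leaving 392 of 492 per arm (79.7%) to enrol
- 100/165 = 60.6%, leaving 65 of 165 per arm (39.4%) to enrol

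**How informative?** If placebo counts were also shown:

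- Difference: 0.20 − 0.145 = 0.055
- Standard error: √(0.20 × 0.80/100 + 0.145 × 0.855/100) = √0.00284 = 0.053
- Power of a two-sided 5% comparison at 100 per arm: about 18%

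The expected difference is about one standard error, so what reviewers saw would be mostly noise. That does not make disclosure harmless, since a chance imbalance can influence conduct as readily as a true effect.

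**The case against.** Several stronger readings are tempting, and the protocol does not support them.

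- **The review replaces the DSMB.** Section 5.1.1 omits the DSMB but does not exclude it. The Version 3 text gives it a safety role, and Section 5.1 has it advise on allocation when arms are added. What stands is that the checkpoint is not tied to the DSMB and that the purpose given in Section 5.1 does not list drug safety.
- **Clinicians who enrol and refer patients will see the results.** The text says only that the review is internal. The reviewers are undefined, and the deferred interim monitoring plan might restrict them.
- **AbbVie is the maker of LPV/r, with a commercial stake.** The protocol does not say so. It says that the company reviews the data and must give permission.
- **Placebo will be compared with active drug.** The step names only the monotherapy arms. By-group comparison of adverse events in Section 12.3.2.1 concerns the planned safety analyses, though it makes a placebo column plausible. Without one, HCQ and LPV/r events would still be visible side by side.
- **This is an unplanned look that inflates type I error.** It is planned, with a stated trigger and purpose. Testing at 5% both here and at the end would give an overall error of about 9.2% (target 492) or 7.9% (target 165), but only if this look could declare efficacy. It has no such rule.
- **It contradicts the blinded interim rule outright.** That sentence governs whether to hold an interim analysis, not safety review. The two sit badly together without being a strict contradiction.

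The event counts are also an upper guide, because the trigger is drug administered to 100 patients per arm and some follow-up will be incomplete.

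None of this removes the core. Section 5.1.1 names who reviews by-arm safety data, and following it as written discloses them outside the route that the protocol sets up for interim results.

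**Conclusion.** The point holds as a matter of interim confidentiality. A planned review at 100 per arm would show largely primary-outcome events by arm to the trial team and to an outside company while randomisation continues: about 14.5 to 20 hospitalisations per 100 patients, at 20% of 492 or 61% of 165 per arm. This assumes the protocol's event rate and effect, complete follow-up, and a review that includes the serious adverse events the protocol defines. It does not depend on placebo data being shown.

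The harm is operational bias and loss of confidentiality; no alpha is spent and no sample size changes. It is a cheap improvement, best made before the checkpoint because disclosure cannot be undone.

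**What to change.** In Section 5.1.1, replace the sentence naming the reviewers with: *By-arm safety data after 100 patients per arm are reviewed by the DSMB in closed session. The trial team and AbbVie receive only the DSMB's recommendation on opening the combination arm.* If the company must see data before giving permission, add that it receives either pooled data or by-arm data through a firewalled safety contact with no role in the trial.

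In Section 5.1, add safety to the DSMB's stated purpose so that it agrees with the remit in the Version 3 text.

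The cost is wording in two sections and one agenda item for a DSMB for which the Version 3 text already foresees monthly meetings. The downside is that AbbVie must accept a DSMB recommendation or a firewalled review.
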